### Family-based single dignity intervention

This single intervention will be delivered by a researcher who is experienced in counseling. This intervention will be done based on the protocol introduced by Ho et al., through which, a 60–90-min intervention interview session will take place for each caregiver in a private room in the palliative care center [29]. In this session, caregivers will be asked to answer 12 open-ended questions related to the Ho et al. protocol. The questions focus on eliciting caregivers’ experiences of living with a cancer patient before and after the diagnosis of cancer. Also, these questions will help caregivers to review the beautiful memories of living with a cancer patient and express their hopes, wishes, and desired expectations. The responses to these questions will be audio-recorded and then will be transcribed verbatim in a manuscript for each caregiver. The manuscript will be checked with caregivers and, if needed, corrections will be done. A copy of the manuscript will be delivered to caregivers.

### Expressive writing intervention

This intervention will be done based on the Pennebaker method [39]. Before the intervention, caregivers will be instructed by a trained researcher in order to do this writing. The researcher will receive training on expressive writing by participating in a writing art workshop. Caregivers in this group will be asked to write about a prompt, and they will be instructed to “really let go and explore their very deepest emotions and thoughts.” They will be also told to write about either negative or positive family memories and describe their experiences of caregiving in the present and past time. This writing should be done three times (in a week) lasting 20 min. In that week, the researcher will remind the writing process using a phone call. They are also assured that they do not need to worry about sentence structure or grammar when writing. After 1 week of opportunity for expressive writing, the manuscript of caregivers will be received.

### Combined family-based dignity intervention and expressive writing

For this combined intervention, at first, the session related to family-based dignity intervention will be held and after that, training on expressive writing will be delivered to caregivers. After 1 week from the last session, the manuscript of caregivers will be received.

### Control group

Caregivers in the control group, as well as those in the intervention groups, will receive routine care such as family counseling and meaning therapy. In brief, meaning therapy is an integrative and positive existential approach for counseling and psychotherapy. Details on this therapeutic method are published elsewhere [40].

### Post-trial care

After finishing this study, we will recommend caregivers to receive routine care such as family counseling and meaningful therapy for having good mental health. Also, at the end of the study, we will assess whether combined interventions of family-based dignity and expressive writing or each intervention alone reduce anticipatory grief by 10 points, based on the AGS-13, compared to the routine care as a control intervention. The 10-point decrease or increase is considered a clinically and statistically significant change in anticipatory grief based on the study of Garand et al. [38] and also given the total AGS-13 scores ranging between 13 and 65.

### Anticipatory grief scale

The original form of anticipatory grief scale was designed by Theut et al. to assess anticipatory grief in spouses of Alzheimer’s patients [41]. This form consisted of 27 items measuring anticipatory grief on a Likert scale, ranging from 1 (strongly disagree) to 5 (strongly agree). The items should be summed into a total score ranging from 27 to 135 with a higher score indicating higher levels of anticipatory grief. However, 8 items (2, 5, 8, 11, 19, 22, 26, and 27) have a positive bearing and therefore must be reversed before the total score is calculated. In addition to the total score of anticipatory grief, the score of seven subscales including anger, guilt, anxiety, irritability, sadness, feelings of loss, and decreased ability to function in performing usual tasks can be reached from this scale. In 2019, Holm et al. [42] introduced a short form of AGS containing 13 items and was named AGS-13 (items 1, 3, 4, 7, 10, 15, 16, 18, 20, 21, 23, 24, and 25 of the original form). This scale specifically measures a total score of anticipatory grief in family caregivers of cancer patients and also consists of two subscales, named “Behavioral reactions” and “Emotional reactions,” which capture the behavioral and emotional reactions of grief in caregivers participating in palliative care. To obtain a total score of anticipatory grief in AGS-13, like the original form, the items should be summed into a total score ranging between 13 and 65. Higher scores indicate higher anticipatory grief in caregivers of cancer patients. No item should be reversed before calculating the total score. To increase the data quality obtained from the AGS-13, investigators will give a brief explanation about the questionnaire and its items to participants. Also, we have no concern about the effect of baseline AGE-13 responses on the second and third assessments (1 week and 2 weeks after the interventions) because Holm et al. reported that the questionnaire has sufficient sensitivity that means any true changes in anticipatory grief result in a change in the total score of AGS-13 [42].

### Translation, validity, and reliability of AGS-13

#### Translation

Since the AGS-13 was not used in Iran, we will translate it to Persian based on the method proposed by Guillemin [43]. At first, the permission to use and translate the AGS-13 will be gathered from its developer (Holm et al.) [42]. Then, the English version of the instrument will be translated to Persian by two independent health professionals fluent in English and Persian languages and familiar with the concepts of the questionnaire. After that, an expert panel will assess the translations and select the best translation of each item, and finally, a single form will be produced. Then, the initial Persian form of the tool will be translated back to English by two other qualified persons and the best backward translations will be chosen by the same expert panel afterward. The final backward translation form will be sent to the developer of the tool, to be reviewed for probable inadequacy of words and concepts. Consequently, the confirmed Persian version of the tool will be used for the current study.

#### Validity

Content validity (CV) will be used to assess the validity of AGS-13. The assessment of CV will be done using two qualitative and quantitative methods. In the qualitative method, the opinion of 11 experts in the fields of instrumentation and psychometric measurement, community health nursing, and specialist physicians in the field of psychology and oncology will be received in order to observe and assess grammar, wording, item allocation, and scaling. Then, the quantitative CV will be examined using the Content Validity Ratio (CVR) and Content Validity Index (CVI) [44, 45].

#### Internal consistency

Cronbach’s alpha coefficient will be used to measure the internal consistency of the AGS-13 using SPSS software (version 18).

#### Test-retest reliability

To measure the stability of the AGS-13, 30 caregivers will be asked to fill the scale two times with a 2-week interval. These caregivers will not participate in the main study. Test-retest reliability will be tested using the intra-class correlation coefficient (ICC) with a 95% confidence interval (CI). *P* values less than 0.05 will be considered significant.

#### Other information

Demographic data including age, sex, marital status, education, medical history, and medication will be collected at the baseline.

### Statistical analysis for the quantitative phase

All collected data will be coded and then will be entered into the SPSS software version 18 (SPSS, Inc., Chicago, IL, USA) for performing statistical analysis. To ensure the accuracy of the dataset, it will be double-checked by another investigator. The analyses will be performed on the basis of an intention-to-treat (ITT) approach. Therefore, missing values will be treated according to the last-observation-carried-forward method. The Kolmogorov-Smirnov test will be used to examine the normal distribution of quantitative variables. We will normalize the non-normally distributed variables using log transformation. To detect differences in quantitative and categorical variables between the intervention groups, we will use the analysis of variance (ANOVA) and chi-square test, respectively. To determine the effect of family-based dignity intervention and expressive writing on anticipatory grief, we will use repeated measures ANOVA. In this analysis, the intervention groups (family-based dignity intervention, expressive writing, combined intervention, and control groups) will be considered as the between-subjects factor and the time points (before and 1 week and 2 weeks after the interventions) will be considered as the within-subjects factor. Also, to assess differences between the intervention groups in terms of mean changes of anticipatory grief, the multivariate analysis of covariance (ANCOVA) will be applied by considering baseline measurements and variables different between the groups as covariates. *P* value<0.05 will be considered as a significant level.

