## Introduction

The diagnosis of cancer is an unpleasant and unbelievable experience for every person, and it imposes a high burden on the patient and his/her families [1–3]. As cancer progresses, patients became physically and psychologically weaker, and their dependency on family increases [4]. In addition to the dependency, the caregiving responsibilities of patients are often transferred to family caregivers who are usually spouses, adult children, mother, or father [4, 5]. Therefore, family caregivers, particularly those who take care of dying cancer patients, usually are confronted with several social, physical, and psychological difficulties, which may adversely affect their health [6, 7]. It has been shown that more than 35% of family caregivers experience psychological disorders and feelings of helplessness, hopelessness, and anticipatory grief [8, 9]. This is the reason that caregivers are considered as “second-order patients,” who need supportive care [10].

The religious culture of Iranian caregivers makes a strong relationship between caregivers and patients [11]. For this reason, caregivers look at their responsivities as moral commitment and divine duty [12]. Nevertheless, this religious belief may cause them to hide their needs and caregiving problems [13]. Moreover, there are no specific social organizations in Iran to support caregivers and to diminish their problems [14]. Therefore, family caregivers in Iran, compared with those from developed countries, may be at a higher risk of psychological disorders or anticipatory grief.

Anticipatory grief is one of the important problems among family caregivers [6]. They usually think about the threat of death or separation that can initiate a grief reaction, while the patient is physically present and needed of care [15]. Anticipatory grief is a “safeguard against the impact of a sudden death notice” that helps caregivers to cope with bereavement [16]. However, anticipatory grief is a highly stressful and ambivalent experience that may be a reason for the incidence of psychological distress among caregivers [17, 18]. In addition, this feeling may be transferred to patients and affect their treatment process. Therefore, caregivers should try to control their feelings and refrain from expressing grief for cancer patients [19, 20].

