### Inclusion criteria

We will include caregivers with the following criteria: (1) caregivers who are the first-degree relatives [i.e., parents, offspring, and siblings] of cancer patients and have the most responsibility for caregiving of them during the last 3 months, (2) those who are caregiving of the cancer patients who are dying or critically ill according to the opinion of the treating physician, and (3) caregivers aged ≥18 years.

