### Non-inclusion criteria

We will not include caregivers who have a history of psychological disorders and those who have a history of death among their first-degree relatives. Also, caregivers who are not the first-degree relatives of dying cancer patients and those who have experience of psychological interventions (particularly dignity and expressive writing interventions) during the last 6 months will not be included. Also, we will exclude those caregivers who are not willing to continue each phase (quantitative and qualitative) throughout the study. Figure 1 shows the study flowchart.

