After the random allocation, sessions related to the interventions (family-based single dignity intervention and expressive writing) will take place at the time that will be set with caregivers. To avoid sharing experiences between caregivers, we will try to provide a situation that caregivers do not have contact with each other. For this, we will include a maximum of four caregivers in a day from different rooms of the oncology center in Firozgar hospital (study setting) and we will set a specific time for each caregiver so that there is no possibility of contact and sharing experiences with each other. Also, after discharging the four previously included caregivers from the hospital, we will include the other new four caregivers to minimize their contact. On the other hand, recruitment will be stopped until discharging the four previously included caregivers. Caregivers in all intervention groups will receive routine care such as family counseling and meaning therapy, and they will be asked not to participate in other psychotherapy programs. Since the interventions used in the current study are interview-based, we cannot blind the investigators and caregivers to the interventions.

Before the intervention session and 1 week and 2 weeks after the interventions, anticipatory grief will be assessed by a 13-item anticipatory grief scale (AGS-13). The mean of AGE-13 score at baseline and throughout the study will be considered as the main outcome variable. The diagram for Standard Protocol Items: Recommendations for Interventional Trials (SPIRIT) is shown in Fig. 2.

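### Last observation carried forward does not follow from intention-to-treat: it modestly dilutes the effect at the planned loss, and as a blanket rule it would carry scores past a patient's death

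*Protocol article*

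**What the plan says.** Under Statistical analysis for the quantitative phase, the article states: "The analyses will be performed on the basis of an intention-to-treat (ITT) approach". The next sentence draws a consequence from this: "missing values will be treated according to the last-observation-carried-forward method". The article names no other treatment of missing scores. For the effect of the interventions, "we will use repeated measures ANOVA", with an ANCOVA of change adjusted for baseline alongside it.

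Other places that bear on this:

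- **Study design for the quantitative phase:** the AGS-13 is taken at three points: "Before the intervention session and 1 week and 2 weeks after the interventions".
- **Inclusion criteria:** participants care for "the cancer patients who are dying or critically ill according to the opinion of the treating physician".
- **Introduction:** anticipatory grief is described as a reaction that arises "while the patient is physically present and needed of care".
- **Sample size calculation:** 10% drop-out is expected in each group.
- **Post-trial care:** the change looked for is 10 points on a scale that runs from 13 to 65.
- **Non-inclusion criteria:** "we will exclude those caregivers who are not willing to continue each phase". If this is applied after randomisation, it also has to be reconciled with ITT.

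The article does not say what happens to a score when the patient dies before an assessment. The baseline data listed under Other information are caregiver characteristics, and no date of the patient's death is mentioned.

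**The concern.** The inference from ITT to LOCF is wrong. ITT keeps every randomised caregiver in the assigned arm. It does not supply a missing score. LOCF supplies one by assuming that nothing changed after the last visit. A caregiver who misses both follow-ups is then analysed as having exactly zero change, in a trial built to detect change over that same short interval.

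The second difficulty is specific to this population. Where the patient dies before week 1 or week 2, anticipatory grief as the Introduction describes it can no longer be measured. The score is then arguably undefined rather than merely missing. A blanket LOCF rule makes no distinction and enters the last score from before the death as a week-1 or week-2 outcome.

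At stake are dilution of a real effect and, under less favourable conditions, a difference between arms that the interventions did not cause.

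**Working it through.** **How much loss the plan expects.** The plan's own figure reproduces: n = 2 × (1.96 + 0.842)² × 23.1² / (78.17 − 64.49)² = 44.77, so 45 per group, and 45 / 0.90 = 50. A 10% loss is therefore about 5 of 50 caregivers per group.

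**Assumptions, not in the article.** SD 11.1 on the AGS-13 (close to the plan's 23.1 scaled from 27 to 13 items: 23.1 × 13/27 = 11.1), correlation 0.6 between visits, and loss at random. Half of those missing at week 2 are already missing at week 1. Any treatment effect is fully present at week 1. In expectation the SD and correlation do not alter the bias. They do alter the type I error.

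**Dilution with equal loss.** Let E be the true effect and m the share missing. The half missing from week 1 contribute their baseline, so no effect. The half missing only week 2 contribute week 1, so the full effect. LOCF then estimates E × (1 − m/2).

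- m = 10%: 10 × 0.95 = 9.5
- m = 20%: 10 × 0.90 = 9.0

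If baseline is carried forward for everyone missing, LOCF estimates E × (1 − m): 9 at 10%, 8 at 20%, 7 at 30%. An effect only partly present at week 1 falls between the two cases.

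**False difference with unequal loss and drift.** Let all arms drift by d points a week, with no true effect. Carrying baseline forward loses 2d. Carrying week 1 forward loses d. The average lost per missing caregiver is 1.5d, so the expected difference (arm A minus arm B) is −1.5 × d × (m_A − m_B).

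- d = 3, 30% against 10%: −1.5 × 3 × 0.20 = −0.90
- d = 3, 40% against 10%: −1.5 × 3 × 0.30 = −1.35
- d = 5, 30% against 10%: −1.5 × 5 × 0.20 = −1.50

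The arm with more loss looks better when drift is upward. The sign reverses if the loss is on the other side.

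**Type I error by simulation** (50 per arm, 4000 trials per setting, ANCOVA on the week-2 score, no true effect):

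| Loss in the two arms | Drift per week | Type I error with LOCF |
|---|---|---|
| 10% / 10% | 0, 3, 5 | 5.0%, 4.4%, 4.6% |
| 10% / 30% | 0 | 5.3% |
| 10% / 30% | 1 | 4.8% |
| 10% / 15% | 3 | 6.0% |
| 10% / 30% | 3 | about 8% |
| 10% / 40% | 3 | about 11.5% |
| 10% / 30% | 5 | about 13% |

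Over repeated runs at 30% against 10% with drift of 3 to 5 points a week, the bias lay between about 0.8 and 1.6 points and the type I error between about 7 and 14%. ANCOVA on observed scores stayed unbiased, with error near 5%.

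A harsher variant assumes SD 8, baseline carried forward for everyone missing, and a t-test on change. At 30% against 10% loss it gave false differences of 1.0 and 2.0 points, with type I error of 11% and 26%, when scores rose by 5 and 10 points in total.

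**Patient death.** No arithmetic applies. The Inclusion criteria admit caregivers of dying patients, the Introduction ties anticipatory grief to a patient who is present, and the analysis section applies LOCF to every missing value. Read together, a death before an assessment leads to a carried-forward score for a state that has ended.

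**The case against.** The strongest reply is that the harm is small under the plan's own scenario. With 10% loss in each arm, type I error stays near 5%, the estimate moves by half a point to one point out of ten, and the movement is towards no effect. Under the assumed SD, a true 10-point effect was still detected in 99.95% of simulated trials with LOCF. All of this stands.

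A reader might infer several stronger things that the article does not support:

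- **That grief changes from week to week without treatment.** Only the assessments are weekly. The planned two-week test-retest check presumes fair stability.
- **That patient death will be the main reason for missing scores.** This is plausible from the Inclusion criteria, but the article gives no reasons for loss.
- **That LOCF makes the standard errors wrong in every case.** With equal loss and no effect, rejection was 4.4 to 5.0%, and model standard errors agreed with the empirical ones.
- **That LOCF favours the interventions.** The direction depends on which arm loses more and which way scores drift.

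The simulations also remove scores at random, so they do not represent loss caused by death. A mixed model does not settle that case either, because it too implies values after dropout. A separate rule for death is needed.

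Finally, a journal article may leave deaths by arm and sensitivity analyses to a fuller document, so their absence is no finding. What remains is the rule that the article does fix and the reason it gives for it.

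**Conclusion.** The concern holds as a change that should be made, not as a flaw that invalidates the trial. LOCF is fixed in the text on a justification that does not support it. It assumes zero change after dropout where change is the object of study, and it takes no account of the patient's death.

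At the planned 10% loss per arm, a 10-point effect shrinks to about 9.5 (9 if only baseline is carried forward) and type I error stays near 5%. At 20% the figures are 9.0 and 8. A false difference of about 0.8 to 1.6 points, with type I error of about 7 to 14%, arises only when unequal loss and drift occur together, as with 30% against 10% and 3 to 5 points a week.

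Those loss and drift values, the SD of 11.1 and the correlation of 0.6 are assumptions. The harsher variant shows that the error can be larger under other choices. A reader might conclude that the trial's false-positive rate is already compromised. The article gives no loss imbalance or drift from which that would follow.

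**What to change.** 1. Delete the sentence that derives LOCF from ITT. State instead that all randomised caregivers are analysed in their assigned arm, using every observed AGS-13 score.
2. Use a likelihood-based mixed model for repeated measures, with arm, time, arm-by-time and baseline AGS-13, and state that it is valid if scores are missing at random. The MIXED procedure in SPSS fits it. With baseline as a covariate, a caregiver with no follow-up score remains in the randomised set but adds no information on change.
3. State that no score is carried past the patient's death, and record the date of death so that this can be applied.
4. Say whether the exclusion of caregivers unwilling to continue applies after randomisation and, if so, reconcile it with ITT.

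The cost is a change of analysis wording, one extra data field that has to be collected while the trial runs, and slightly larger standard errors than LOCF would report. No further participants are needed.

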### Sample size calculation

Considering the type I error of 5% (*α*= 0.05) and type II error of 20% (*β*= 0.20, power = 80%) and anticipatory grief score as the key variable, we manually, without the use of any software, calculated the required sample size using the following formula [36, 37]:
$$ n=\frac{2\left[{\left(\mathrm{a}+\mathrm{b}\right)}^2\times {\upsigma}^2\right]}{{\left({\mu}_1-{\mu}_2\right)}^2} $$

*n* = sample size in each group

*μ*_1_ = mean for anticipatory grief score in group 1 (considered as 78.17 based on the study of Garand et al. [38])

*μ*_2_ = mean for anticipatory grief score in group 2 (considered as 64.49 based on the study of Garand et al. [38])

*σ* = variance (SD) for the mean of anticipatory grief score, which was considered as 23.1 (the average SDs reported for anticipatory grief score in the 2 groups of Garand et al. study [38]).

*a* = conventional multiplier for alpha = 0.05 that was 1.96

*b* = conventional multiplier for power = 0.80 that was 0.842

Overall, based on the formula and given a 10% drop-out in each group, we will need a sample size of 50 caregivers for each intervention group.

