### Limitations

Despite using validated questionnaires for the assessment of anticipatory grief, misclassification of caregivers in terms of this variable cannot be fully excluded. Since the interventions used in the current study are interview-based, we cannot blind the caregivers to the interventions. Although we try to control for variables different between the groups in statistical analysis, we cannot entirely exclude the effects of residual confounders or differences on our findings.

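### Two data-driven rules leave the ANCOVA's extra covariates and the scale of AGS-13 unfixed, and a log-scale result would not directly answer the 10-point question

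*Protocol article*

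**What the plan says.** All of this is in the Protocol article.

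- **Covariates** (Statistical analysis for the quantitative phase). ANOVA and chi-square tests are used to detect differences between the groups, and P<0.05 is the only significance level given. The ANCOVA of mean changes is then fitted "by considering baseline measurements and variables different between the groups as covariates". The Limitations section repeats the intention: "Although we try to control for variables different between the groups in statistical analysis". No covariate other than the baseline measurement is named.
- **Candidates** (Other information). Six baseline variables are listed: age, sex, marital status, education, medical history and medication.
- **Scale** (Statistical analysis for the quantitative phase). Quantitative variables are checked with a Kolmogorov-Smirnov test, and then: "We will normalize the non-normally distributed variables using log transformation". AGS-13, the main outcome, is not exempted.
- **Effect question** (Post-trial care). The trial will assess whether the interventions "reduce anticipatory grief by 10 points, based on the AGS-13, compared to the routine care as a control intervention", on a scale running from 13 to 65.
- **Repeated measures ANOVA.** This analysis, which the protocol uses to determine the effect of the interventions, has group and time as its only factors.

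**The concern.** **Covariates.** If randomisation is sound, a baseline difference between arms is a chance event. A rule that admits variables because they differ therefore selects on imbalance. It can bring in a variable unrelated to grief and leave out a strong predictor that happens to be balanced. The adjusted model is then known only after the baseline table has been seen.

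**Scale.** A normality test on the variables decides whether the outcome is analysed in points or in logs. The linear model needs roughly normal residuals, not normal raw scores, and about 45 analysable caregivers per arm already gives comparisons of means fair protection. The trial's criterion is additive, in AGS-13 points, while a log-scale effect is multiplicative. If the test rejects, the model's estimate and the protocol's own threshold are on different scales.

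**Working it through.** **1. The plan's own figure.** Inputs from Sample size calculation: "conventional multiplier for alpha = 0.05 that was 1.96"; "conventional multiplier for power = 0.80 that was 0.842"; means 78.17 and 64.49; SD 23.1; 10% drop-out.

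n = 2 × (1.96 + 0.842)² × 23.1² / (78.17 − 64.49)² = 2 × 7.851 × 533.61 / 187.14 = 44.77, so 45 per group. 45 / 0.90 = 50. The stated 50 is reproduced, and nothing below changes it. The assumed mean of 78.17 lies above the AGS-13 maximum of 65, so these inputs say nothing about the shape of the AGS-13 distribution. Every statement about shape below is an assumption.

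**2. How often chance changes the ANCOVA.** With k independent baseline variables, each tested at 0.05 and with no true imbalance, P(at least one differs) = 1 − 0.95^k.

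| k | Chance that the covariate set changes |
|---|---|
| 4 | 18.5% |
| 6 (as named) | 26.5% |
| 8 | 33.7% |

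**3. What this does to the error rate.** A simulation under the null used four arms of 50, baseline always in the model, six independent normal covariates and 4,000 runs per setting. The covariates' common coefficient was 0.105, 0.21 or 0.266 on an outcome of unit variance, so together they explained 6 × 0.105² = 7%, 6 × 0.21² = 26% or 6 × 0.266² = 42% of it.

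| Variance explained by covariates | Selected at P<0.05 | All six fixed | Baseline only |
|---|---|---|---|
| 7% | 0.049 | 0.058 | 0.049 |
| 26% | 0.042 | 0.051 | 0.050 |
| 42% | 0.035 | 0.051 | 0.049 |

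Selection keeps the test at or below 5%, and it becomes conservative as the covariates become prognostic. The baseline-only and selected models disagreed on significance in 0.7%, 1.6% and 1.8% of runs.

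**4. Points against ratios.** On the log scale a 10-point fall has no single size:

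- from 55: ln(55/45) = 0.20
- from 30: ln(30/20) = 0.41

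In the other direction, one ratio of 0.75 against control is 60 × 0.25 = 15 points at a control mean of 60, 10 points at 40, and 6.25 points at 25. A log coefficient becomes a point difference only at a chosen reference mean, and the protocol gives no such step. In addition, the ANCOVA is described in terms of mean changes. If the change itself is the variable to be logged, a zero or negative change has no logarithm.

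**5. Could the trigger fire, and would the log help?** Sums of 13 correlated 1-to-5 items were simulated (400 runs per setting, mean skewness from about 0 to −0.5) and tested with the Kolmogorov-Smirnov test in its estimated-parameter (Lilliefors) form. The protocol does not say which form is meant, or whether arms are pooled.

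| N tested | Raw score rejected | Logged score rejected |
|---|---|---|
| 50 | 7–25% | 27–52% |
| 200 | 25–90% | 90–100% |

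As one left-skewed example, a Beta(5,2) variable stretched to 13–65 has mean 13 + 52 × 5/7 = 50.1, SD 8.3 and skewness −0.60. After the log its skewness is about −1.1.

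**The case against.** Several points on the other side are sound.

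- **Reach of the covariate rule.** It touches only the ANCOVA. The repeated measures ANOVA carries no covariates, and the ANCOVA always includes the baseline measurement. Only the demographic and medical covariates are open. This stands.
- **Error rate.** A reader might infer that data-driven selection inflates type I error. The simulation does not support that for the covariate rule. For the scale, raw and log ANCOVA in an assumed null model were significant in 5.3% and 5.7% of runs and disagreed in 2.2%. The 6.6% significant on at least one scale would need someone to pick the better result, whereas the protocol's rule selects one scale.
- **The 10-point question.** A reader might also infer that a log analysis makes it unanswerable. That is too strong. Raw arm means remain available, and the Post-trial care section does not tie the 10-point assessment to a log coefficient. What stands is that the log model does not give the answer directly and that no conversion is stated.
- **Inference and assumptions.** The covariate clause does not itself say P<0.05; this is read from the neighbouring sentences. The six variables are unlikely to be fully independent. The documents report no AGS-13 distribution, and with right skew a log could help. No document shows that age, sex or education predicts AGS-13.

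An unseen statistical analysis plan does not remove the point, because the protocol commits to both rules instead of leaving them open.

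**Conclusion.** The point holds within these limits. The protocol fixes two analysis choices badly.

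First, the ANCOVA's covariates beyond baseline depend on chance imbalance. About one trial in four would change the model this way, given six independent variables and a 0.05 trigger. The consequence is an adjusted model that is not fixed in advance and some lost precision if the covariates are prognostic, with a slightly conservative test.

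Second, a normality test can move AGS-13 to a log scale in both analyses, and the resulting ratio does not directly give the 10-point difference. That 10 points can be 0.20 or 0.41 log units is plain arithmetic. How often the test would reject, and whether the log would worsen the shape, rest on assumed distributions.

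The trial remains interpretable and its sample size is unaffected. Both rules should nonetheless be replaced before outcome data are seen.

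**What to change.** Amend the statistical analysis section as follows.

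- Keep baseline AGS-13 as a covariate in the ANCOVA. Name any further covariates now, on prognostic grounds, from the variables already collected, and use them whatever the baseline table shows. If none can be justified, say that baseline AGS-13 is the only covariate.
- Drop significance testing of baseline differences as a rule for choosing covariates, and bring the sentence in Limitations into line.
- Analyse AGS-13 in raw points whatever a normality test shows, so that the group coefficient is the point difference named in the Post-trial care section. Remove the Kolmogorov-Smirnov and log rule for this outcome.
- Check residuals, and report a bootstrap or robust-standard-error interval as a sensitivity analysis.

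The cost is a few sentences. No extra data, visits or participants are needed.
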